### Study participants and selection criteria

STRONG participants include 60 community-dwelling elderly people aged 90 years or over recruited from a geriatric nursing home (Los Nogales-Pacífico, Madrid, Spain). All participants received a comprehensive medical examination.

The inclusion criteria for STRONG are:

- Age: 90 years or over.

- Planning to stay in the same nursing home during the study.

- Able to ambulate, with or without assistance.

- Able to communicate.

- Informed consent: Must be capable and willing to provide consent.

The exclusion criteria for STRONG are:

- Acute or terminal illness.

- Myocardial infarction in the past 3 months.

- Not capable to ambulate.

- Unstable cardiovascular disease or other medical condition.

- Upper or lower extremity fracture in the past 3 months.

- Severe dementia.

- Unwillingness to either complete the study requirements or to be randomised into control or training group.

- Presence of neuromuscular disease or drugs affecting neuromuscular function.

Figure 1 illustrates the participant flow from recruitment to randomisation.

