### Statistical analysis

For group comparisons at baseline (usual care *vs *intervention), we will analyse continuous variables with a Student's *t *test (or its non-parametric equivalent) for unpaired data, and Chi-square tests for nominal data. We will adjust multiple comparisons for mass significance [38,39]. We will also examine the differences between drop-outs and participants who remained in the study. We will analyse the data according to the intention-to-treat principle [40]. We will handle missing data due to drop-outs or non-compliance using multiple imputation methods. To fully appreciate the potential influence of missing responses, we will perform sensitivity analysis.

We will use a two-factor (group and time) analysis of variance (ANOVA) with repeated measures to assess the training effects on the primary outcomes [muscular strength, daily physical functioning (Tinetti scale, Barthel index, ambulation ability) and QOL and well-being] and secondary study outcomes (anthropometry and PA levels). For each outcome variable we will report the effect size and the level of significance corresponding to the main group (between-subjects), time (within-subjects) and interaction (group × time) effects. In order to prevent type I error, we will perform post hoc comparisons (pre *vs *post by group) only when a significant interaction effect is present. The level of significance will be set to = 0.05.

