## Discussion

Up to April 2009, 58 nonagenarians living in the aforementioned geriatric nursing home meet all the eligibility criteria. Forty-eight of them originally gave their written permission to participate in the study in the previous months. Of these 48 persons, six who were allocated to the control group finally refrained from participating in the study. One participant assigned to the training group had to drop-out from the program after having completed only one training session due to eye surgery. The number of participants who are currently participating in the study within the control and intervention group is n = 12 (2 men and 10 women, mean (SD) age: 92 (3) years, range 90 to 97 years) and n = 18 (3 men and 15 women; mean age: 92 (2) years, range 90 to 96 years) respectively. All these 30 participants successfully completed all of baseline evaluations, included all the strength and functional tests. Of the total of 24 training sessions that we programmed for each participant in the training group, the 19 subjects who are currently in this group have performed an average of 10 sessions, with a mean adherence of 87%. Main reasons for missing a training session were mild upper respiratory tract infections, falls (at night, out of training sessions) or simply forgetting. We noted no major health problem (included absence of falls) associated with the baseline strength tests or training sessions, expect mild muscle pain in some participants.

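### Six people left after allocation to control against one from training; the numbers allocated are not stated, and the promised missing-data analyses are not aimed at this loss

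*Protocol article*

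**What the plan says.** The status report in the Discussion starts from the eligible residents ("58 nonagenarians living in the aforementioned geriatric nursing home meet all the eligibility criteria") and those who consented ("Forty-eight of them originally gave their written permission to participate in the study in the previous months"). It then names two kinds of loss:

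- in control: "Of these 48 persons, six who were allocated to the control group finally refrained from participating in the study";
- in training: "One participant assigned to the training group had to drop-out from the program after having completed only one training session", because of eye surgery.

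Current membership follows: "The number of participants who are currently participating in the study within the control and intervention group is n = 12" for control and 18 for training, 30 in all. Completed baseline evaluation is reported for these 30 only. A later sentence gives training a different size: "the 19 subjects who are currently in this group have performed an average of 10 sessions".

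The Statistical analysis section states the principle: "We will analyse the data according to the intention-to-treat principle [40". It adds multiple imputation for drop-outs and non-compliance, a comparison of drop-outs with those who stayed, and a sensitivity analysis for missing responses. It states neither the imputation assumption nor the kind of sensitivity analysis. Study design places random allocation after baseline measurement. The exclusion criteria include "Unwillingness to either complete the study requirements or to be randomised into control or training group".

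**The concern.** Randomisation protects the comparison only for the people who were randomised. The six refusals are described as coming from people already allocated to control. The single named training loss has a medical reason, and no refusal is reported from training. Loss of this pattern can depend on the allocation itself, and those who leave may differ in motivation, function or expected course from the controls who stay.

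Three features of the document make this more than a routine missing-data matter:

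- The allocated numbers by arm are not given and the training count is inconsistent, so the loss cannot be stated exactly.
- Baseline completion is reported only for those still taking part. If the six have no baseline data, an imputation model has little to work with except the remaining controls and will largely reproduce them.
- The exclusion criterion on unwillingness does not say that it stops applying at randomisation, and people who refrain after allocation fit its wording.

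At stake is a biased control mean, and hence a biased training effect, on every primary outcome.

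**Working it through.** **The plan's own figures.** Sample size and statistical power gives a 4-point Tinetti difference, SD 5, α 0.05 (two-sided assumed) and power above 80%. With z values 1.96 and 0.84, n per group = 2 × (1.96 + 0.84)² × 5²/4² = 24.5, so 25, as stated. The total of 60 follows from 50 × 1.20. The 20% is therefore an allowance on total recruitment.

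**Flow counts (Discussion).**

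- Control: 12 current + 6 left = 18.
- Training: 18 current + 1 left = 19.
- Accounted for: 18 + 19 = 37 of 48 consenters; 48 − 37 = 11 have no fate stated in the text.
- Training sex split: 3 men + 15 women = 18, which supports 18. The 19 is probably 18 plus the drop-out, but it is described as current membership.

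**Loss by arm.** The denominators 18 and 19 are derived, not reported. They hold only if none of the 11 was allocated. Counting only the seven named leavers:

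| Assumption about the 11 | Control | Training | Fisher p |
|---|---|---|---|
| None allocated | 6/18 = 33.3% | 1/19 = 5.3% | 0.042 |
| None allocated, 19 current plus the drop-out | 6/18 = 33.3% | 1/20 = 5.0% | 0.038 |
| All 48 allocated 24:24 | 6/24 = 25.0% | 1/24 = 4.2% | 0.097 |
| All 11 to control | 6/29 = 20.7% | 1/19 = 5.3% | not run |
| All 11 to training | 6/18 = 33.3% | 1/30 = 3.3% | not run |

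Control loss is thus 21–33% and training loss 3–5% under any split. The direction is stable; the p-value is not. Overall loss is 7/37 = 18.9% if none of the 11 was allocated.

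**Effect on the control mean.** Let the remaining controls have mean m, let the six have mean m + δ, and let N be the number allocated to control. Imputation that takes the six to be like the rest returns m. The mean over all allocated is [(N − 6) × m + 6 × (m + δ)]/N = m + δ × 6/N, so the error is δ × 6/N. The document gives no δ, so these are illustrations:

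- N = 18: δ = 2 gives 0.7; δ = 4 gives 1.3; δ = 6 gives 2.0 points.
- δ = 4: N = 24 gives 4 × 6/24 = 1.0; N = 29 gives 4 × 6/29 = 0.8.

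For δ = 4 the shift is 0.8/4 to 1.3/4, about 21% to 33% of the target effect. The sign is unknown. If the six would have scored lower than the others, the imputed control mean is too high and the training effect is understated; if higher, it is overstated.

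**The case against.** The strongest reply is that the plan already has the right elements: intention-to-treat, imputation, a comparison of drop-outs with stayers, and a sensitivity analysis. The detail of such analyses is commonly left to a full protocol or analysis plan. That stands as far as the missing detail goes. It does not answer a lopsided loss that this article itself reports and to which it ties none of those elements.

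Several stronger readings are tempting and are not supported:

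- *The 30 are the analysis set, so intention-to-treat is already broken.* The 30 are a count of people taking part in April 2009. Nothing declares them to be the analysis set.
- *The imputation planned is known to be inadequate.* Its model and assumed mechanism are not stated. The weakness applies if it assumes that leavers resemble stayers.
- *The difference in loss is established at p = 0.04.* That figure needs the derived denominators; an even split of all 48 gives 0.10.
- *The planned 20% maximum has been exceeded.* That figure is for the whole trial, and 7/37 is within it. Only the control arm on its own lies above 20%.
- *Eleven consenters have been lost.* They may not have been allocated yet, and the flow diagram, which is not available here, may account for them. It cannot remove the conflict between 18 and 19 in the text.
- *The six left because they were disappointed with their arm, or were removed as ineligible.* No reason for leaving is given, and nothing shows the exclusion criterion being used in this way.

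**Conclusion.** The point holds in a limited form and is worth acting on. The document shows loss after allocation of six in control against one in training: 21–33% against 3–5%, depending on how many of the 11 other consenters were allocated. It gives two sizes for the current training group and leaves open whether the leavers have baseline data. The stated principle is sound, but an imputation that treats the control leavers like the controls who stayed would not correct withdrawal that depends on allocation. With an assumed 4-point difference, the control mean would be off by about 0.8–1.3 Tinetti points against a 4-point target, in an unknown direction. That size rests on the assumed difference and on the unstated number allocated to control. The case for change does not depend on the Fisher p-value.

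**What to change.** - State the number allocated to each arm, say what became of all 48 consenters, and reconcile 18 with 19 in training. State whether the seven leavers completed baseline.
- Define the intention-to-treat set as everyone allocated, analysed as allocated, including the six controls and the one training drop-out. Say that the unwillingness criterion applies only before randomisation.
- Ask the leavers to allow the 8-week assessment alone. Observed outcomes are worth more than any imputation.
- Specify the promised sensitivity analysis as a delta-adjusted imputation of the missing control outcomes, for example from −4 to +4 Tinetti points, and report the tipping point at which the conclusion changes. Set corresponding ranges for the other primary outcomes.

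The cost is some wording, one extra analysis, and a request that the leavers may decline. Confidence intervals may be wider.

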## Conclusion

The increase in life expectancy together with the dramatic decrease in birth rates in industrialized countries calls the attention to health care systems and public health policymakers to focus attention on promoting healthy lifestyle in the highest sector of the population pyramid. Our study attempts to improve functional capacity and QOL of nonagenarians by implementing an individualised aerobic and strength training program in a geriatric residential care. Results from STRONG will help to better understand the potential of regular PA for improving the well being even in persons aged 90 years or over.

## Abbreviations

1RM: one repetition maximum; ACSM: American College of Sports Medicine: ADLs: activities of daily living; AHA: American Heart Association; ANOVA: analysis of variance; BMI: body mass index; FAC: Functional Ambulation Classification; MMSE: Mini-Mental State Examination; MVPA: moderate-to-vigorous physical activity; PA: physical activity; QOL: quality of life; RCT: randomised controlled trial; RPE: rate of perceived exertion; SF-12: Short Form-12 items.
